### 2.2. Study registration

This study trial has been registered on the Clinical Research Information Service (http://cris.nih.go.kr) with an ID of No. KCT0005254.

### 2.3. Participants

Individuals who were diagnosed as SCD were eligible for the study. Subjects who visited the hospital due to persistent cognitive worsening and were diagnosed with SCD after dementia work-ups are consecutively recruited. The dementia work up included detailed neuropsychological test battery, MRI, and routine blood sampling for syphilis, thyroid function, vitamin B deficiencies, and apolipoprotein epsilon genotyping. The inclusion criteria were as follows (Table 2): Age ≥ 60 years of age; Existence of persistent self-reported cognitive complaints; Normal performance (above −1.0 standard deviation [SD] of norms) on all subtests of neuropsychological test battery named Seoul Neuropsychological Screening Battery (SNSB);^[4]^ Clinical dementia rating (CDR) score of 0;^[5]^ Agreement to participate in the study and could visit the hospital for annual evaluations. The exclusion criteria were the following: Mild cognitive impairment (MCI) or dementia; Brain lesions known to cause cognitive impairment (tumor, stroke, or subdural hematoma); Any neurological disorders such as Parkinson’s disease, Huntington’s disease, epilepsy, or normal pressure hydrocephalus; Major psychiatric disorders such as uncontrolled depression, schizophrenia, alcoholism, or drug dependency; Abnormal blood laboratory findings such as abnormal thyroid function, low vitamin B12 or low folate, or positive syphilis serology, and; Hearing loss that is impossible to perform phone-based cognitive tests.

**Table 2 T2:** Eligibility criteria.

Inclusion criteria
age ≥ 60 yr of age
existence of persistent self-reported cognitive complaints
normal performance (≥−1.0 standard deviation of norms) on all subtests of SNSB
CDR score of 0
agreement to participate in the study and could visit the hospital for annual evaluations
**Exclusion criteria**
MCI or dementia
brain lesions known to cause cognitive impairment (tumor, stroke, or subdural hematoma)
any neurological disorders such as Parkinson’s disease, Huntington’s disease, epilepsy, or normal pressure hydrocephalus
major psychiatric disorders such as uncontrolled depression, schizophrenia, alcoholism, or drug dependency
abnormal blood laboratory findings such as abnormal thyroid function, low vitamin B12 or low folate, or positive syphilis serology
hearing loss that is impossible to perform phone-based cognitive tests

CDR = clinical dementia rating, MCI = mild cognitive impairment, SNSB = Seoul neuropsychological screening battery.

### 2.4. Recruitment

We will recruit 80 participants with SCD (Fig. 1). The researcher explains the aim and the methods of the study and will obtain informed consent from potential participants before the collection of medical information.

**Figure 1. F1:**
[figure not shown]
Study flowchart.

### 2.5. Intervention

No study related pharmacological/ non pharmacological interventions are planned. For participants who progressed to dementia, regardless of amyloid positivity, they can be treated with acetylcholinesterase inhibitors according to physician’s practical decision.

### 2.6. Neuropsychological tests

SNSB includes Korean version of the mini-mental state examination (K-MMSE),^[6]^ CDR, Korean version of activities of daily living,^[7]^ attention (digit span test), language (Boston naming test, tests for comprehension/repetition/fluency), visuospatial function (Rey Complex Figure Test), verbal and visual memory function (Seoul Verbal Learning Test and Rey complex figure test recall test), and frontal executive function (contrasting program, go-no-go, Controlled Oral Word Association Test, and Stroop test).^[4]^ Age, sex, and education-specific norms based on normal controls were used to interpret the SNSB results. Scores ≥ 16th percentile, which were compared to–1 SD of the norm, were defined as normal. Severity of the cognitive complaints were assessed using a self-rated scale named cognitive failures questionnaire (total score 0–100, higher total score means more cognitive complaints).^[8]^ Using a self-report questionnaire, “informant also report a cognitive decline of the participant,” “subjective concern about the cognitive decline,” and “symptom’s onset after 65 years of age” were assessed at baseline and follow-up evaluations.

### 2.7. Outcome measures

The primary outcome measure is K-MMSE score changes at the endpoint. The secondary outcome measures include demographic data, baseline and follow-up SNSB subdomain scores, self-report questionnaires, HCT scores, brain MRI markers, florbetaben PET positivity, quantitative regional amyloid depositions using PET scans, and clinical progression rates.

All participants will undergo baseline neurologic examinations, neuropsychological tests named SNSB, brain MRIs, blood labs, and florbetaben PET scans for amyloid depositions. PET findings are interpreted using a visual rating scale named brain amyloid plaque load and rated as positive amyloidosis with a brain amyloid plaque load score of 2/3.^[9]^ Quantitative neuroimaging analysis will be performed.

At baseline, questionnaires for SCD, amyloid PET scans, brain MRIs including 3 dimensional-T1 imaging, plasma amyloid beta values are examined. Telephone-based HCT at home are performed every 6 months during the study period. Annual follow-up evaluations include detailed neuropsychological tests, physical and neurologic examinations, and physician’s assessments for clinical progression. Brain MRI and plasma amyloid beta values are assessed at baseline and 24 months later (Table 1).

Clinical progression to mild cognitive impairment or dementia will be assessed at the final visit. The cognitive tests were administered by a trained neuropsychologist. Participants with CDR score ≥ 0.5 or Korean version of activities of daily living score ≥ 0.43 were considered to have progressed to MCI or dementia.

### 2.8. Neuroimaging analysis

Brain MRI are performed using a 3.0-Tesla scanner (GE Medical Systems, Milwaukee, WI), including fluid attenuated inversion recovery (FLAIR), susceptibility weighted image, and 3-dimensional (3D) T1-weighted images. The white matter hyperintensities (WMHs) are rated using a visual rating scale of axial FLAIR images. In brief, periventricular WMHs and deep WMHs are evaluated separately and rated as minimal (grade 1), moderate (grade 2), or severe (grade 3).^[10]^ Lacunes are defined as small lesions (3–15 mm in diameter), hyperintense on *T*2-, and hypointense on *T*1-weighted images, with a perilesional halo on FLAIR.^[11]^ Cerebral cortical microbleeds are defined as round and homogeneously low-signal lesions <10 mm in diameter on susceptibility weighted image.^[11]^ Hippocampal atrophy is rated on coronal *T*1-weighted images using Scheltens visual rating scale.^[12]^ The number of lacunes, number of microbleeds, degree of WMH, and degree of hippocampal atrophy will be measured by a trained neurologist blinded to the data.

Florbetaben (18F) PET scans are acquired following the standardized protocol.^[13]^ Using PET scans, a whole brain visual interpretation is performed by a trained doctor in nuclear medicine who is blinded t the patient diagnosis. In addition, quantitative neuroimaging analyses are performed using PET scans and MRI 3D-*T*1 images. First, amyloid depositions were assessed using MATLAB version 2013a and SPM8 (http://www.fil.ion.ucl.ac.uk/spm/software/spm8). Individual 3D *T*1-weighted MRI scans are estimated and co-registered into corresponding PET images. A volume-based template, incorporating 90 regions-of-interest, is aligned to individual *T*1-weighted MRI scans. The voxels of florbetaben PET images were scaled using the mean uptake value in the cerebellar gray matter to calculate the standardized uptake value ratio (SUVR), and partial volume corrections are performed. The mean SUVR values are calculated as a global SUVR. Second, the MRI volumetric analysis are performed using AQUA 2.0 program (Neurophet, South Korea). The details of the MRI segmentation and data analysis were described elsewhere.^[14]^ A normative dataset is obtained using the East-Asian dataset described in a previous study,^[15]^ and the adjusted volume (z score) corrected with total intracranial volume, age, and sex is measured.

### 2.9. Plasma amyloid beta values

Plasma amyloid beta values are measured using the Multimer Detection System-oligomeric Aß (MDS-OAß) method.^[16]^ In brief, the inBloodTM™ OAß test (People Bio Inc., Gyeonggi-do, Republic of Korea) will be used to quantify MDS-OAß values in heparin vacutainer tubes. Higher values indicate more amyloid oligomeric tendencies with vigorous amyloidosis. Plasma amyloid beta values are assessed at baseline and 24 months.

### 2.10. Sample size calculation

We assumed that a 3.5-point difference in K-MMSE assessment scores (the primary outcome measure between the A + SCD and SCD groups) after 48 months would be significant. With an alpha value set at 0.05, a beta value of 0.9 (90% power), and a SD value of 4.5 for change, a total of 36 participants were required for each study group. Assuming a discontinuation rate of 10% during the 48-month study, the total calculated sample size required for the study was 80 participants.

### 2.11. Statistical analysis

Independent *t* test or nonparametric Mann–Whitney *U* test (based on normal distribution patterns) is used for comparison of continuous variables such as baseline demographics and clinical characteristics between A + SCD and A − SCD participants. Chi-square tests will be used to compare categorical variables between the 2 groups. analysis of covariance corrected for baseline scores would be used to compare cognitive changes between the 2 groups. All statistical analyses are performed using SPSS (version 18.0; SPSS Inc, Chicago, IL). *P* values < 0.05 is considered to indicate statistically significant differences.

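### Section 2.11 names no test for ordered MRI grades; its chi-square rule, the natural reading, would ignore their order and cost some power for secondary markers

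*Protocol article*

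**What the plan says.** The protocol article, section 2.11, gives two type-based rules for comparing A+ with A− participants outside the cognitive outcomes.

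- The t test, or Mann-Whitney where the data are not normal, "is used for comparison of continuous variables such as baseline demographics and clinical characteristics".
- For everything categorical, "Chi-square tests will be used to compare categorical variables between the 2 groups".

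Cognitive change has its own rule, an ANCOVA adjusted for baseline score. Ordered categories are not mentioned, and no list says which variables count as categorical.

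Section 2.8 (Neuroimaging analysis) defines the grades. Periventricular and deep WMH are each "rated as minimal (grade 1), moderate (grade 2), or severe (grade 3". Hippocampal atrophy is graded on a visual scale, with the number of grades not given. Section 2.8 adds that "degree of WMH, and degree of hippocampal atrophy will be measured" by a blinded neurologist.

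Section 2.7 lists these markers among the secondary outcomes: "HCT scores, brain MRI markers, florbetaben PET positivity".

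**The concern.** A three-grade rating is neither continuous nor a cognitive change. A reader applying section 2.11 as written would therefore most naturally use chi-square for WMH and hippocampal grades. Pearson chi-square gives the same P value however the grades are arranged. It spreads its power over every kind of difference between the groups instead of concentrating on a shift toward worse grades.

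The Discussion states a directional hypothesis: A+ participants are expected to show more atrophic change. For the hippocampal grade, a test that uses the order is closer to that question. At stake is a modest loss of sensitivity for secondary markers in a study of about 80 people. There is also some freedom to choose the test after the grades have been seen.

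**Working it through.** **1. The plan's own figure.** Section 2.10 sizes the study on K-MMSE: difference 3.5, SD 4.5, alpha 0.05 (taken as two-sided), power 90%.

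- Normal approximation: n per group = 2 × (1.960 + 1.282)² × 4.5² / 3.5² = 2 × 10.507 × 20.25 / 12.25 = 34.7, so 35.
- The t-based calculation gives 35.73, so 36, as stated.
- Allowing for 10% discontinuation: 72 / 0.9 = 80, as stated.

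The figure reproduces. It concerns K-MMSE only; no power figure is given for the MRI grades. It does supply the group sizes used below.

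**2. Cost of ignoring order, in general.** Suppose the whole difference lies along the trend. A 1-df test with 80% power at alpha 0.05 has noncentrality 7.85. The same noncentrality on a general chi-square gives:

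| Grades | df | Power |
|---|---|---|
| ordered test | 1 | 80% |
| 3 | 2 | 71% |
| 4 | 3 | 65% |
| 5 | 4 | 60% |

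**3. Cost at this study's size.** The article gives no grade distributions, so those used here are assumptions. A− proportions were set, and the A+ group was shifted by a common odds ratio (OR): each cumulative odds in A− is divided by the OR. Example with A− at 60/30/10% and OR 2.5:

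- Grade 1: odds 0.6/0.4 = 1.5; 1.5/2.5 = 0.6; proportion 0.6/1.6 = 37.5%.
- Grades 1 and 2: odds 0.9/0.1 = 9; 9/2.5 = 3.6; proportion 3.6/4.6 = 78.3%.
- A+ is therefore 37.5/40.8/21.7%.

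Each setting was simulated 20,000 times, comparing Pearson chi-square with tie-corrected Mann-Whitney, two-sided 0.05. With A− at 60/30/10%:

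| OR | 40 vs 40: chi-square / Mann-Whitney | 36 vs 36 | 56 A− vs 24 A+ |
|---|---|---|---|
| 2 | 28% / 36% | 25% / 32% | 26% / 32% |
| 2.5 | 47% / 57% | 42% / 52% | 43% / 51% |
| 3 | 63% / 73% | 57% / 68% | 58% / 66% |
| 4 | 84% / 90% | 79% / 87% | 78% / 85% |

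Two other assumed A− distributions (75/20/5% and 40/40/20%) were run with the same splits. Over all three, the loss runs from 3.4 points (75/20/5%, 56 vs 24, OR 2: 25.2% against 28.6%) to 11.3 points (75/20/5%, 40 vs 40, OR 3: 54.9% against 66.2%). Linear-by-linear trend stays within about 2.5 points of Mann-Whitney.

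A separate illustration, not built on a common OR, used 65/25/10% against 40/38/22%. With 36 vs 36, power is about 48 to 49% for chi-square and 59% for Mann-Whitney. With 48 A− and 24 A+, it is 46% and 55%.

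**4. More grades.** With five assumed grades (35/35/20/8/2%), the loss is about 11 to 25 points, for example 54% against 77% at OR 3 with 40 vs 40. This applies only if the hippocampal scale has that many grades.

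**5. Validity.** With no true difference, chi-square rejected in 3.7% to 5.2% of runs over all the step 3 and step 4 settings. It does not inflate the error rate, even with sparse upper grades.

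**6. A case that goes the other way.** With 60/30/10% against 35/60/5% (non-monotone), 40 vs 40, chi-square has about 70% power, Mann-Whitney 43% and linear-by-linear 31%.

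**The case against.** The strongest reply is that the article never says WMH or hippocampal grades go to chi-square. It names Mann-Whitney in the same paragraph, a numeric grade could reasonably be given that test, and a condensed article may leave the assignment to the full plan. This stands in part: the assignment is an inference. But section 2.11 ties Mann-Whitney to continuous variables and offers only chi-square for the rest. The point is therefore about how a stated rule fits, and not only about missing detail.

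Three further objections hold.

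- The distributions and shifts are assumed, and the ranking reverses for a non-monotone pattern.
- No aim or hypothesis names WMH, and atrophy has a continuous measure that needs no chi-square: "the adjusted volume (z score) corrected with total intracranial volume, age, and sex is measured".
- The study was not sized on these grades.

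A reader might also infer that sparse grades make chi-square unreliable, or that its result cannot show which group is worse. Neither is supported. Expected counts below 5 are common in some settings, yet the error rate stays at or below about 5%. Direction can be read from the grade counts by group, although the P value does not carry it.

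**Conclusion.** The point holds as a minor clarification. Read as written, section 2.11 most naturally sends the ordered MRI grades to Pearson chi-square, which is valid but ignores order. For a monotone shift with three grades and 72 to 80 participants, the cost is roughly 3 to 11 percentage points of power. That range rests on assumed grade distributions, proportional-odds shifts with OR 2 to 4, and a two-sided 0.05 level. It is larger if the hippocampal scale has more grades.

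A reader might infer that the plan misassigns these variables outright or that the study's main conclusion is weakened. The documents support neither. No sentence makes the assignment, and "The primary outcome measure is K-MMSE score changes at the endpoint", with cognitive change analysed by ANCOVA. The primary analysis, the sample size and the volumetric z-score analyses are untouched.

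**What to change.** Add one sentence to section 2.11: ordered MRI grades (periventricular WMH, deep WMH, visual hippocampal atrophy) are compared between A+ and A− with the Mann-Whitney test already named, or with a linear-by-linear trend test, reporting the direction and an effect size such as a rank-based measure or an odds ratio. State that chi-square is kept for unordered categories.

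Set this before the grades are compared by amyloid status, so that the test is not chosen after seeing the results. If Mann-Whitney is already intended, the sentence simply says so. No new data are needed. The one statistical cost is lower power for non-monotone differences; tabulating the grade counts by group would keep such a pattern visible.

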## Abstract

**Methods::**

Data will be collected from a prospective observational cohort study conducted in South Korea. Eighty participants with SCD aged ≥ 60 years are eligible for the study. All participants undergo annual neuropsychological tests and neurological examinations, bi-annual brain MRI scans and plasma amyloid markers, and baseline florbetaben Positron Emission Tomography scans. The amyloid burden and regional volumes will be measured. Cognitive and biomarker changes will be compared between the amyloid-positive SCD and amyloid negative SCD groups. Validation would be performed to assess reliability and feasibility of HCT.

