## 2. Methods

### 2.1. Study design

This study is a longitudinal observational cohort based study performed at a university-affiliated dementia clinic from May 2020 to December 2025. A total of 80 elderly participants with SCD who presented with a complaint of persistent cognitive decline are planned to be enrolled at baseline in a single center and undergo annual follow up evaluations during 48 months (see Table 1).

**Table 1 T1:** Data collection.

Assessments	Screening	Baseline	12/36 months	24 months	48 months
Eligibility	**√**				
Demographics	**√**				
Comorbidity	**√**	**√**			
Concomitant medication	**√**	**√**	**√**	**√**	**√**
Blood chesmistry	**√**				
Plasma amyloid beta		**√**		**√**	
SNSB	**√**		**√**	**√**	**√**
Self-report questionnaire		**√**	**√**	**√**	**√**
Brain MRI	**√**			**√**	
Florbetaben PET		**√**			
Physical examination	**√**	**√**	**√**	**√**	**√**
Vital signs		**√**	**√**	**√**	**√**
Neurologic examination	**√**	**√**	**√**	**√**	**√**
HCT*		**√**	**√**	**√**	**√**
Physician’s judgements of progression			**√**	**√**	**√**

HCT = home-based cognitive test, PET = positron emission tomography, SNSB = Seoul neuropsychological screening battery.

* Home-based cognitive tests (HCT) are performed every 6 months during the study period.

First, we have developed a HCT (score range 0–30, higher scores indicate better cognitive function) composed of 20 questions that can be assessed using phone-calls. Second, neuropsychological tests, blood samplings, physical and neurologic examinations, brain MRIs, florbetaben positron emission tomography (PET) scans, self-report questionnaires are evaluated at baseline. Third, all participants undergo annual follow up neuropsychological tests, physical and neurologic examinations, physician’s history taking to judge clinical progression. All participants should undergo bi-annual brain MRI scans and plasma amyloid beta markers until the end of the study (Table 1). The first participant was enrolled in June 2020, and remaining participants are being recruited.

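### The comparison of cognitive change between non-randomised amyloid groups names only the baseline score as a covariate, so any imbalance in age, sex or education that relates to rate of decline may be misread as an amyloid effect

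*Protocol article*

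**What the plan says.** Section 2.1 sets the design: "This study is a longitudinal observational cohort based study performed at a university-affiliated dementia clinic". Section 2.7 forms the groups from the baseline florbetaben scan, "rated as positive amyloidosis with a brain amyloid plaque load score of 2/3", and fixes the outcome: "The primary outcome measure is K-MMSE score changes at the endpoint". Entry is from age 60 with no upper limit (Abstract and section 2.3).

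Section 2.11 gives the only model for change: "analysis of covariance corrected for baseline scores would be used to compare cognitive changes between the 2 groups". It does not call this model primary, but K-MMSE change is a cognitive change and no other model is offered for it. Demographics appear in section 2.11 only in univariate tests. The t test or Mann–Whitney test "is used for comparison of continuous variables such as baseline demographics and clinical characteristics between A + SCD and A − SCD participants", and chi-square tests serve for categorical variables. Nothing takes an imbalance found there into the outcome model.

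Age, sex and education do appear elsewhere. Section 2.6 says "Age, sex, and education-specific norms based on normal controls were used to interpret the SNSB results", and section 2.8 describes MRI volumes as "corrected with total intracranial volume, age, and sex". Neither adjustment is applied to the K-MMSE change. That outcome is planned in score points, with a 3.5-point difference and an SD of 4.5 in section 2.10.

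**The concern.** Amyloid status is not allocated, so nothing in the design balances the groups on age, sex or education. Adjusting for baseline K-MMSE deals with differences in starting level. It does not deal with differences in the rate of decline that come with age, sex or schooling.

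Univariate baseline tests do not remove confounding. With about 36 per group, a non-significant test cannot rule out an imbalance large enough to matter.

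The aim in section 1.2 is to learn whether amyloid-positive SCD progresses faster, and the Discussion (section 3) links faster decline to amyloid and neurodegenerative pathology. If amyloid-positive participants are older and older participants decline faster, the error favours the study's hypothesis. Recruiting more people would not reduce it.

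**Working it through.** **Inputs from section 2.10:** difference 3.5 points, SD of change 4.5, alpha 0.05, power 90%, 36 per group, 10% discontinuation.

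**Inputs assumed, because the article gives none:** group difference in mean age of 3 to 5 years; extra 48-month K-MMSE loss of 0.05 to 0.15 points per year of age. Nothing was quantified for sex or education.

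**Step 1, the plan's own figure.** With two-sided alpha of 0.05, the normal approximation gives 2 × (1.960 + 1.282)² × 4.5² / 3.5² ≈ 34.7, so 35 per group. With the noncentral t distribution, 35 per group gives power 0.894 and 36 gives 0.902, so 36 is the smallest sufficient number. Allowing for discontinuation, 36 / 0.9 = 40 per group, or 80 in total. The stated sample size reproduces and is not in dispute.

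**Step 2, precision.** SE of the group difference = 4.5 × √(2/36) = 1.06 points.

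**Step 3, bias and type I error.** Bias = (age difference) × (slope per year). Type I error is the two-sided rejection probability at 36 per group when the true amyloid effect is zero and the estimate is shifted by the bias.

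| Age gap (years) | Slope (points per year) | Bias (points) | Share of 3.5 | Type I error |
|---|---|---|---|---|
| 3 | 0.05 | 0.15 | 4% | 5.2% |
| 5 | 0.05 | 0.25 | 7% | 5.6% |
| 3 | 0.10 | 0.30 | 9% | 5.9% |
| 5 | 0.10 | 0.50 | 14% | 7.5% |
| 5 | 0.15 | 0.75 | 21% | 10.7% |

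A steeper assumed slope of 0.2 with a 5-year gap would give 1.0 point (29% of the target) and 15.3%. This lies outside the range above and shows only how the result moves.

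**Step 4, does adjustment remove the bias?** A simulation used 4,000 runs per case, 36 per group and no true amyloid effect. Only age differed between groups and affected change.

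| Case | Baseline-only: bias, rejection | With age, sex, education: bias, rejection |
|---|---|---|
| 3 years × 0.10 | −0.27, 5.7% | 0.02, 4.7% |
| 5 years × 0.10 | −0.48, 7.1% | 0.00, 4.6% |
| 5 years × 0.20 | −0.97, 14.6% | 0.00, 5.2% |

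The negative sign means more apparent decline in the amyloid-positive group.

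**Step 5, cost in power.** The residual SD is 4.5 × √(1 − R²y), where R²y is the share of outcome variance that the covariates explain. The SE is multiplied by √(1/(1 − R²g)), where R²g is the share of group membership that they explain. Four covariates are charged to the degrees of freedom. For a true 3.5-point difference at 36 per group:

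| R²g | R²y | Power |
|---|---|---|
| 0 | 0 | 0.90 |
| 0.10 | 0 | 0.87 |
| 0.20 | 0 | 0.83 |
| 0.10 | 0.10 | 0.90 |
| 0 | 0.10 | 0.93 |

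**The case against.** The strongest reply has four parts.

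- **Condensed text.** Section 2.11 is a short paragraph in an article. It does not say that baseline is the only covariate, and a fuller list could sit in an analysis plan that is not shown. This has some force. Still, the article names a covariate set for the comparison of change, so the point concerns a stated analysis and not merely absent detail.
- **Prognostic reading.** Sections 1.1 and 1.2 can be read as asking whether amyloid status predicts faster decline. For that question a baseline-only contrast is a legitimate description. This stands, and it is why that model should be kept as a supportive analysis. It does not cover the attribution to pathology in the Discussion.
- **Level versus change.** A reader might infer from the SNSB norms and the MRI z scores that the protocol itself treats age, sex and education as drivers of decline. It does not. Both concern the level of a measure, and neither says anything about the rate of K-MMSE change. Norm-based entry and CDR 0 also limit baseline differences. So the documents leave confounding possible but do not demonstrate it.
- **Size and direction.** No imbalance or slope is documented, only age was quantified, and sex or education could act in the opposite direction. Much of the assumed range is minor against an SE of 1.06. This stands too.

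**Conclusion.** The point holds in conditional form. The stated model can give a confounded contrast if the PET groups differ in age, sex or education and these relate to rate of decline. Under the assumed age gaps and slopes the bias runs from trivial to material, and no assumed case approaches the 3.5-point target by itself.

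Three stronger readings are tempting, and the documents support none of them:

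- That covariate differences will be taken for an amyloid effect. No imbalance is reported, so the most that can be said is that they may be.
- That the study's main question cannot be answered. The prognostic version can be, and a bias of the assumed size blurs the amyloid-specific version without destroying it.
- That adjustment must improve precision. Step 5 shows that it can gain power, leave it unchanged or lose some.

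This is a cheap improvement that should be made. It does not invalidate the plan.

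**What to change.** In section 2.11, pre-specify age, sex and years of education alongside the baseline score in the ANCOVA for K-MMSE change. Report the baseline-only model as a supportive analysis, labelled as prognostic. Fix the covariate list before outcome data are analysed, so that it is not chosen according to the baseline tests or the results.

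No new data should be needed: Table 1 records demographics at screening, and education is required to apply the norms in section 2.6. The cost is a change of wording, three degrees of freedom, and the possible modest power loss shown in step 5 if the covariates track amyloid status without explaining decline.

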## 3. Discussion

In this study, we aim to conduct a longitudinal observational study to assess cognitive and biomarker changes in Korean participants with SCD over the course of 48 months. We will assess whether SCD participants showed different cognitive and biomarker trajectories according to biomarker status. We hypothesize that A + SCD participants would show more cognitive decline and atrophic changes after 48 months. Baseline neurodegenerative changes and amyloid burden are expected to be related with cognitive trajectories in SCD. In particular, neurodegenerations combined with sufficient amyloid depositions above the threshold level would show rapid cognitive progression in SCD participants because existence of the 2 key pathologies indicate later stages of preclinical AD. In addition, in an effort to monitor cognitive declines in SCD participants, we have developed a new HCT as an alternative option of hospital-based in-person neuropsychological tests. Considering that subjects with normal cognition are still reluctant to visiting hospitals for regular in-person cognitive tests and this population generally show lower annual progression rates (5–10% annually) compared with those with MCI/ dementia,^[2,3,17]^ regular cognitive monitoring at home would be clinically helpful to detect cognitive changes in SCD subjects without visiting hospitals for the cognitive tests.

We are now conducting recruitments of the participants and baseline database will be completed by 2023. Despite of a few limitations that other biomarkers assessing combined tau, alpha synuclein, or TAR DNA-binding protein 43 pathologies are not evaluated, our study have several strengths as followings: Participants are consecutively recruited in South Korea using a comprehensive neuropsychological test battery and undergo various biomarker evaluations, allowing us to clarify cognitive and biomarker trajectories of SCD participants. All participants undergo baseline amyloid PET scans, regular brain MRI scans, and plasma amyloid beta markers to quantitatively measure amyloid burden and neurodegenerative changes.

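### The K-MMSE ANCOVA pools one residual variance while nothing secures equal groups; if A+ is the smaller group and only a subset of it declines, the 95% interval will be too narrow

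*Protocol article*

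**What the plan says.** The primary outcome is change in K-MMSE at the endpoint (section 2.7). For cognitive change, section 2.11 says "analysis of covariance corrected for baseline scores would be used to compare cognitive changes between the 2 groups". It names no robust or unequal-variance method. The t test or Mann–Whitney choice in the same section is described for variables such as baseline characteristics.

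Section 2.10 plans with one spread for both groups, "a SD value of 4.5 for change", and equal groups: "a total of 36 participants were required for each study group".

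On how the groups arise, section 2.3 says "Subjects who visited the hospital due to persistent cognitive worsening and were diagnosed with SCD after dementia work-ups are consecutively recruited". Section 2.4 sets a target of 80 with no quota by amyloid status, and section 2.7 assigns amyloid status from the baseline PET reading. The expected A+ share is not given.

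The Discussion states the hypothesis: "We hypothesize that A + SCD participants would show more cognitive decline and atrophic changes after 48 months". It adds that rapid progression is expected where neurodegeneration accompanies sufficient amyloid, and it cites 5–10% progression a year for this population as a whole.

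**The concern.** An ordinary ANCOVA estimates a single residual variance and uses it for both groups. With equal group sizes, the standard error of the group difference is right even if the spreads differ. With unequal sizes it is right only if the spreads are equal. Consecutive recruitment with groups formed by PET leaves the sizes to chance.

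Equal spread is also open to doubt. Everyone enters with normal scores on all SNSB subtests and CDR 0. If the 3.5-point mean gap arises because some A+ participants fall a long way while the others stay stable, A+ is a mixture and its SD of change is larger. If A+ is also the smaller group, the pooled standard error gives too little weight to the noisier group mean. The interval for the main comparison is then too narrow, and its P value too small.

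**Working it through.** **1. The plan's own figure.** Inputs from section 2.10: difference 3.5, SD 4.5, alpha 0.05 (taken as two-sided), power 90%, 1:1.

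- Normal formula: 2 × (1.960 + 1.282)² × (4.5/3.5)² = 34.7, so 35 per group.
- With the t distribution, 35 per group gives 89.4% power and 36 gives 90.2%.
- 72/0.9 = 80.

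The figure of 36 per group and 80 in total reproduces.

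**2. Formulas for the standard error.** Let s₊, s₋ be the SDs of change and n₊, n₋ the completers, with n₊ + n₋ = 72.

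- True variance of the difference: s₊²/n₊ + s₋²/n₋.
- Pooled variance of the difference: [(n₊−1)s₊² + (n₋−1)s₋²]/70 × (1/n₊ + 1/n₋).
- Approximate coverage: 2Φ(1.96 × pooled SE/true SE) − 1.

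These leave out the baseline covariate. Step 5 gives the simulation check with the covariate in the model.

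**3. Spread implied by the plan's 3.5 and 4.5 if a share p of A+ declines (p is an assumption).** Each decliner loses D = 3.5/p. The mixture adds m = p(1−p)D² to the A+ variance. Hold the average variance at 4.5², so the two variances sum to 40.5. Then s₊² = (40.5 + m)/2 and s₋² = (40.5 − m)/2.

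Example, p = 0.5: D = 7 and m = 0.25 × 49 = 12.25. So s₊ = √26.375 = 5.14 and s₋ = √14.125 = 3.76. At 22:50:

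- Pooled: (21 × 26.375 + 49 × 14.125)/70 = 17.8; 17.8 × (1/22 + 1/50) = 1.165; SE 1.079.
- True: 26.375/22 + 14.125/50 = 1.481; SE 1.217.
- Ratio 0.887; coverage 91.8%.

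| p of A+ declining | SD A+ / A− | 14:58 | 22:50 | 36:36 | 43:29 |
|---|---|---|---|---|---|
| 34% (1 − 0.9⁴) | 5.65 / 2.93 | 82.1% | 88.0% | 95.0% | 97.2% |
| 50% | 5.14 / 3.76 | 89.5% | 91.8% | 95.0% | 96.3% |
| 70% | 4.78 / 4.20 | 92.9% | 93.7% | 95.0% | 95.6% |
| 100% (uniform shift) | 4.50 / 4.50 | 95.0% | 95.0% | 95.0% | 95.0% |

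**4. Letting A− progress too, so that the overall rate meets the Discussion's 5–10% a year.** Assumptions: a progressor loses 7 points, the within-person SD is 2.5, and the gap stays at 3.5, so p₊ − p₋ = 0.5. The overall four-year rate is R = 1 − (1 − rate)⁴, which is 18.5% at 5% a year and 34.4% at 10%. With A+ share f, p₋ = R − 0.5f and p₊ = p₋ + 0.5. Each variance is 6.25 + 49p(1−p).

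Example, 5% a year at 22:50: p₋ = 0.185 − 0.5 × 22/72 = 0.033 and p₊ = 0.533. The SDs are 4.30 and 2.79, the pooled SE is 0.848 against a true 0.997, and coverage is 90.5%.

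Over A+ shares of 20–35%:

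- 5% a year: SD ratio 1.3–1.65, coverage 90–91%.
- 7.5% a year: SD ratio 1.1–1.3, coverage about 93%.
- 10% a year: SD ratio 1.0–1.1, coverage 94–95%.

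**5. Does the remedy work?** The baseline-adjusted ANCOVA was simulated with 10,000 runs per scenario, SD ratios of 1 to 3, and splits from 14:58 to 43:29. The error rate of a nominal 5% test with HC3 standard errors stayed between 4.3% and 6.0% throughout. With the pooled standard error at 22:50 it was 9.7% at ratio 1.5 and 12.1% at ratio 2. At 36:36 the pooled version stayed at 4.8–4.9%. This shows how each standard error behaves when spreads differ; it is not a forecast of false positives in this study.

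**The case against.** The strongest reply is that the article states nothing false. It names a standard analysis, and the choice of standard error is commonly left to an analysis plan, which is not shown. That stands in part: the absence of a robust method is not an error in itself. It remains worth raising because the method for the primary outcome is named, and its validity leans on either equal spread or a balance that this recruitment cannot guarantee.

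Four stronger readings are tempting, and the document does not support them.

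- **That the interval and P value are bound to be wrong.** Both unequal sizes and unequal spread are needed. The document gives neither the A+ share nor group-specific SDs.
- **That the hypothesis itself implies greater A+ spread.** It concerns the mean. A uniform shift leaves the spreads equal. The sentence about neurodegeneration accompanying amyloid makes a declining subset plausible, no more.
- **That false positives are inflated if amyloid has no effect.** In the argument above, the unequal spread comes from the mean gap. Remove the gap and that source of unequal spread goes with it.
- **That the t tests share the problem.** They are described for baseline-type variables, do not bear on the main comparison, and are not fixed to the equal-variance form.

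A scenario in which half of A+ and no A− progress also deserves caution. At A+ shares of 20–35% it means 10–17.5% progressing overall in four years, below the 18.5–34.4% implied by the cited annual rate. Bringing the rate into line moves coverage up to about 90–95%.

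**Conclusion.** The point holds conditionally. If A+ is the smaller group and its decline is concentrated in a subset, the pooled ANCOVA interval undercovers: about 88–92% at 22:50 when 34–50% of A+ decline, and about 90–95% at A+ shares of 20–35% when A− also progress at the cited overall rate. A more extreme split of 14:58 takes the first pair of figures to 82–90%. The distortion vanishes at 36:36 or under a uniform shift, and turns conservative if A+ is the larger group (96–97% at 43:29).

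The harm is mainly to interval coverage, and to the P value when the groups truly differ in spread. The figures rest on 72 completers and on assumed A+ shares, declining shares and, in the second check, a 7-point loss with a within-person SD of 2.5. This is a worthwhile and inexpensive improvement to the analysis. The sample size arithmetic is not in question.

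**What to change.** Keep the baseline-adjusted comparison of K-MMSE change. Prespecify, before the 48-month data are analysed, that its standard error, interval and P value will use HC3 heteroscedasticity-consistent standard errors, or a model with a separate residual variance for A+ and A−. Report the SD of change in each group.

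This takes about two sentences and no extra participants. The interval will be wider where A+ is smaller and more variable: in the 34% case at 22:50, the true SE of 1.274 against a pooled 1.010 means about 26% wider. That is the uncertainty the pooled version would have hidden. If the spreads prove equal, the loss is at most a few percent of width.
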